### Allocation concealment

Participants, research assistants (RAS) and intervention providers would not know to which group the participants will be assigned. The allocation sequence will be concealed in a sequentially numbered, sealed, and opaque envelope until treatment assignment.

### Blinding

The outcome evaluators are paediatric nurses who are not working in the study hospitals and will be blinded to the study groups. To ensure blinding, participants will be advised not to disclose their group assignment to outcome evaluators. However, due to the nature of the intervention, it is not possible to blind participants and intervention providers. This is an open-label trial with only patient-outcome assessors being blinded so emergency unblinding will not occur.

### Intervention procedures

Guided by Beck’s cognitive model [50], the content and dose of CBI are determined by reviewing international guidelines on CBI [48, 50, 65], and the findings of the systematic review and meta-analysis [66]. Beck’s model describes how thought, feeling, and behaviour interact. Hence, CBI helps identify and modify maladaptive thoughts and behaviour and develops coping skills. Intervention content and strategies for the experimental group will be tailored to the child’s age and health conditions and include psychoeducation, guided discovery or Socratic questioning, discussion, drawing/painting or writing, and play supplemented with home-based practices.

### Experimental group

The experimental group will receive five weekly face-to-face sessions (30–35 min each). The intervention will be delivered by two psychologists with master’s degree who have clinical and research experience in CBI. The contents include (1) an introduction to CBI, (2) identifying, evaluating, and challenging maladaptive thoughts, beliefs and behaviour, (3) behavioural activation, (4) practising deep breathing exercises, and (5) reassessing goals or treatment plans, and encouraging participants to maintain changes.

The intervention will be delivered in the hospital before the children undergo chemotherapy to avoid excessive fatigue and increase their engagement with the interventions. Additionally, to establish a strong family support system and enhance intervention delivery, parents or primary caregivers of the child will be invited to attend the introduction of the first session, the summary of each session, and whenever else necessary. However, the role of the parents/caregivers is only to facilitate the intervention delivery, such as providing information when needed.

To enhance the retention rate, interventions will be delivered during participants’ medical appointments at the hospitals. In addition, each participant will be provided with an appointment card containing the date and time of the next CBI appointment, and the RA will remind them with a phone call 2 days before the next appointment. The participants will continue receiving the usual psychosocial care provided by the nurses in the paediatric oncology ward.

### Control group

The control group will receive the usual psychosocial care such as information and health education about the course of the illness and treatments provided by the nurses in the paediatric oncology ward. Additionally, the RA will offer them attention every week for 30 min about treatment adherence and other concerns. Parents will be invited to attend if they wish to do so.

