**Methods:**

A single-blinded, parallel-group, two-arm, repeated measure randomised controlled trial will be conducted. Eighty children aged 8 − 18 years with haematological malignancy receiving chemotherapy will be recruited and randomly assigned to experimental or control groups. The experimental group will receive five sessions of introducing cognitive-behavioural intervention, identifying and modifying maladaptive thoughts and behaviour, behavioural activation, practising deep breathing exercises, reassessing goals or treatment plans, and encouraging participants to maintain changes. Each session will be conducted face-to-face for 30–35 min a week. The control group will receive usual care. The outcomes will be measured at baseline, post-intervention, and one month after the intervention using the Revised Child Anxiety and Depression Scale and Paediatric Quality of Life Inventory Generic Core Score 4.0.

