## Methods

### Objectives

The objectives of this study are to evaluate whether a theory-based CBI achieves (1) reduced anxiety and depression and (2) improved quality of life post-intervention in the experimental group compared to the control group receiving usual care.

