### Study design

This trial is designed as a multi-centre, assessor-blinded, two-arm parallel-group, repeated measure randomised controlled trial (RCT). The protocol for this trial was registered at ClinicalTrials.gov (NCT05270655). A multi-centre trial helps recruit adequate and representative participants and thus, improves the generalisability of the study findings [58].

The schedule of enrolment, interventions and assessments of the study protocol follows the Standard Protocol Items: Recommendations for Interventional Trials (SPIRIT) Figure (Fig. 1) and SPIRIT Checklist (Additional File 1) [59].

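### The objective and abstract call the comparator usual care, but controls also receive weekly research-assistant attention, so the randomised contrast is not the stated one

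*Protocol article*

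**What the plan says.** All references are to the protocol article.

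- **Abstract, Methods:** "The control group will receive usual care".
- **Objectives:** the effects on anxiety, depression and quality of life are to be judged "in the experimental group compared to the control group receiving usual care".
- **Control group:** the section starts with ordinary ward care: "The control group will receive the usual psychosocial care such as information and health education about the course of the illness and treatments". It then adds a second component: "Additionally, the RA will offer them attention every week for 30 min about treatment adherence and other concerns". Parents may attend if they wish.
- **Experimental group:** five weekly face-to-face sessions of 30–35 minutes, given by two master's-level psychologists. For background care, "The participants will continue receiving the usual psychosocial care provided by the nurses in the paediatric oncology ward".
- **Study design:** two parallel arms.
- **Sample size:** d = 0.7 on anxiety (the smallest value in a cited range of 0.7 to 3.9), 80% power, 5% significance and 15% attrition, giving 80 participants, 40 per group.

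No section describes the weekly contact as part of existing ward practice, and none calls the comparator an attention control.

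**The concern.** The objective fixes the effect that the conclusion will be about. Here it names one contrast while the description of the control arm sets up another. The two agree only if half an hour of weekly contact with a research assistant has no effect on the outcomes, and the protocol does not claim that.

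The protocol's own argument makes a nil effect hard to presume. The Background section links poor treatment adherence to worse quality of life. Adherence is the named topic of the weekly contact, and quality of life is a secondary outcome. The contact is also open to the child's other concerns, which could plausibly bear on anxiety and depression.

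What is at stake is the reading of the result, above all a null one. Under the objective as worded, no difference would be reported as CBI being no better than usual care, which the trial does not test. Someone who reads only the abstract would not know that the control arm received anything extra.

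**Working it through.** **Step 1. What each arm receives**

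| | Experimental | Control |
|---|---|---|
| Usual psychosocial care from ward nurses | yes | yes |
| CBI | five weekly sessions, 30–35 min, psychologist | no |
| Research-assistant attention | not described | 30 min every week, number of weeks not stated |

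The Control group section introduces the attention with a word of addition, after usual care has been described, and assigns it to a different person (research assistant, not nurse). The plain reading is that it is not part of usual care.

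**Step 2. The two contrasts**

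Let U be the mean benefit under usual care alone, U+A under usual care plus attention, and U+C under usual care plus CBI.

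- Stated contrast: S = (U+C) − U
- Randomised contrast: R = (U+C) − (U+A)
- Therefore S = R + a, where a = (U+A) − U is the effect of the attention.

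The trial estimates R. Estimating a needs a group on usual care alone, and there is none. S is therefore recoverable only by assuming a value for a. If a = 0, S = R. If a > 0, R is smaller than S, so the trial understates the effect over usual care.

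**Step 3. Contact time**

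CBI: 5 × 30 to 5 × 35 = 150 to 175 minutes. Control: 30 minutes a week for an unstated number of weeks. Five weeks would give 5 × 30 = 150 minutes, but five is an inference.

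**Step 4. The planned sample size**

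Inputs from the Sample size section: d = 0.7, power 0.80, attrition 15%. The Data analysis section gives a two-sided 5% level. A two-sample t-test (noncentral t) needs 33.02 per group, rounded up to 34. Inflated for attrition, 34 / (1 − 0.15) = 34 / 0.85 = 40 per group, 80 in total. The plan's figure reproduces exactly, so there is no arithmetic error.

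**Step 5. Illustration only: power if the effect against this comparator were below 0.7**

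Two assumptions are needed, and the documents support neither: (i) d = 0.7 is an effect over usual care alone; (ii) the attention itself is worth a = 0.1 to 0.3 SD. Then R = 0.7 − a. With 34 evaluable per group, the noncentrality parameter is R × √(34/2).

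| a (assumed) | R | Noncentrality | Power |
|---|---|---|---|
| 0 | 0.7 | 2.89 | 81% |
| 0.1 | 0.6 | 2.47 | 68% |
| 0.2 | 0.5 | 2.06 | 53% |
| 0.3 | 0.4 | 1.65 | 37% |

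The Sample size section does not say what comparators the cited studies used. If 0.7 came from an attention-controlled study, no power is lost on this ground.

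**The case against.** The best defence is that nothing is hidden. The Control group section states the contact openly, the abstract and objective are one-line summaries in a condensed article, and neither says usual care alone. Controls do receive usual care, so the label is incomplete rather than false. A contact-based control is also a legitimate design, and often a more demanding one. If attention helps, the bias is towards the null, so a positive result would also support superiority over usual care, with only its size understated. The Discussion makes its recommendation conditional on CBI proving effective and acceptable and does not name usual care as the benchmark.

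Much of this stands. The design needs no defence, and the risk of misreading falls mainly on a null result and on the size of a positive one. It does not remove the conflict, though. This is not a detail left to a fuller document: the article gives both descriptions, they differ, and the objective governs what is concluded.

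A reader might go further and infer several things that the documents do not support:

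- **That the trial is underpowered.** This needs both assumptions in Step 5.
- **That the trial isolates CBI content beyond attention.** The provider also differs (psychologist against research assistant), and full matching of contact time is inferred because the number of control weeks is not given.
- **That adherence is discussed only with controls.** The CBI sessions include reassessing goals or treatment plans, and the Background offers beliefs that lead families to abandon treatment as an example of the thinking CBI addresses. A clean separation of content cannot be shown.
- **That the trial registration carries the same error.** The registry record is not at hand.

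**Conclusion.** The point holds as a mislabelled comparator. The stated contrast, CBI against usual care, is not the one randomised, and with two arms it cannot be estimated without assuming the effect of the attention. What the trial estimates is psychologist-delivered CBI plus usual care against usual care plus weekly 30-minute research-assistant attention.

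The direction of the gap follows if attention has any benefit: the effect over usual care is then understated. Its size cannot be obtained from the documents. The 80% power statement is arithmetically right and holds if d = 0.7 applies against this comparator. The range from 81% down to 37% shows sensitivity under assumptions and is not a finding against the sample size. The conclusion rests on reading the weekly contact as an addition to usual care, which the Control group section supports and no other section contradicts.

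This should be corrected because it changes what may be concluded and costs little. It is not a reason to alter the design.

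**What to change.** - In the abstract, the objective and the eventual conclusions, name the comparator as usual care plus weekly 30-minute research-assistant attention.
- Limit the conclusion to that contrast. Do not report a null result as no better than usual care, and say that a positive estimate may understate the effect over usual care alone.
- Note beside the contrast that the provider differs between arms, so a difference is not attributable to CBI content alone.
- Add to the sample-size statement that the 80% power is conditional on d = 0.7 applying against this comparator.

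**Cost:** a few phrases of text, with no change to either arm, the sample size or the analysis. The downside is a narrower claim. The Trial status section puts completion in November 2022, so the wording is best settled before results are interpreted.

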### Outcomes and measurements

#### Primary outcome

Anxiety will be assessed using the anxiety subscale of the self-report 25-items Revised Child Anxiety and Depression Scale (RCADS) (α = 0.91 for anxiety scale) in the original study [67], before the intervention (T0, baseline), immediately after the intervention (T1, at 6 weeks) and one month after completion of the intervention (T2, at 10 weeks). In this study, the Amharic version of the RCADS will be used. The Amharic version of the scale exhibited satisfactory validity and reliability in our other study (*α* = 0.95 and *α* = 0.96 for the anxiety sub-scale and total scale respectively) [unpublished data]. Each item will be rated on a four-point Likert scale (0–3), and the total raw anxiety score ranges from 0 to 45 [68]. To calculate the total anxiety score, the raw scores will be converted into *T*-scores, with *T*-scores of ≥ 65 to 70 and ≥ 70 being borderline and above the clinical threshold, respectively [69]. A higher anxiety score corresponds to higher levels of anxiety.

#### Secondary outcomes

For the secondary outcomes, depression and QOL will be assessed at T0, T1, and T2. The level of depression will be assessed using the depression subscale of the RCADS (*α* = 0.80 for the depression scale in the original study) [67], and *α* = 0.94 for the Amharic version in our study [unpublished data]). A higher score reflects higher depression.

QOL will be measured using a child-report PedsQL™ 4.0 GCS for ages (8 − 12 and 13 − 18 years) [70]. The Amharic version of the scale demonstrated good reliability and validity in our other study (α = 0.96) [unpublished data]. To calculate the total score, each item will be scored on a five-point Likert scale (0–4), and the 0 − 4 scale items will be reversely scored and linearly transformed to 0–100 [71]. A higher score indicates high QOL.

#### Other measures

Participants’ demographic and clinical characteristics will be recorded at baseline using a demographic and clinical datasheet. The overall study process is summarised in Fig. 2.

**Fig. 2 Fig2:**
[figure not shown]
Study procedures adapted from consolidated standards of reporting trials (CONSORT) flow diagram [72]

### Data analysis

The analysis will be conducted using Statistical Package for the Social Sciences (IBM SPSS statistics 26). To check discrepancies in data entry, the principal investigator and a RA will independently enter the coded data twice into SPSS. While categorical data will be summarised using frequencies and percentages, continuous data will be summarised using means, standard deviations, median and interquartile ranges depending on normality distribution. Depending on the types of data and normality distribution, the characteristics of the groups will be compared using independent t-tests, Mann–Whitney U tests, Chi-square tests, and Fisher’s exact tests. Outcome analysis will be conducted as an intention-to-treat analysis. Missing value analyses will be conducted to determine the need for multiple imputations. A generalised estimation equation (GEE) model will be applied to determine the intervention effect between the groups in terms of a group, time, and group*time interaction. Variability in effect will be assessed by performing a sub-group analysis. Given that this trial is studying a low-risk or no-risk intervention, there are no stopping rules or plans for interim analyses. The significance level will be determined at 5% (two-sided) for all statistical tests.

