## Background

Haematological malignancies include malignancies of the blood, bone marrow, and lymph nodes. Leukaemia, lymphoma, and myeloma are the most common types of paediatric cancer all over the world [1–3]. In Ethiopia, evidence shows that more than 50% of childhood cancers are haematological malignancies [4, 5].

The course of childhood cancer causes various stressful symptoms among children [6]. The diagnosis, course of treatment such as painful medical procedures and chemotherapy side effects, and challenges in social life such as missing the opportunity to play with friends, separation from family members, and school absence are major stressors among children [7, 8]. Although most paediatric cancer patients experience various psychological problems, anxiety and depression are among the most frequently reported problems [9, 10]. Childhood cancer also significantly impedes their quality of life (QOL) [11–16].

Poorly managed anxiety and depression significantly impact QOL and survival status [17, 18]. Unmanaged anxiety predicts fatigue [7], anticipatory pain, nausea and vomiting during the subsequent medical procedures [19] and increases off-therapy anxiety [20]. Poorly treated depression impairs relationships and psychological functioning [21], increases the burden of symptoms and mortality [9], and affects motivation to change behaviour and evidence suggests these patients are less likely to adhere to treatment [22]. Non-adherence to treatment including chemotherapy decreases prognosis increases relapse [23, 24], morbidity and hospital readmissions [17] and treatment costs, and has a negative impact on QOL [25]. Likewise, poor QOL is associated with emotional, behavioural, and social problems such as difficulty establishing or maintaining friendships and poor school performance [26].

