In this study, we developed a CBI for children with haematological malignancies guided by Beck’s cognitive model [50]. The model describes the associations among cognition, emotion, and behaviour [47]. Distorted thoughts and unhelpful coping strategies often cause emotional problems such as anxiety and depression [51–53]. For instance, in Ethiopia, most patients experience extreme stress as they believe that there is no hope of childhood cancer being cured with modern medicine. They abandon treatment because they believe religious and spiritual therapies, or alternative forms of treatment such as visiting traditional healers and using holy water, are more effective [54, 55]. Thus, CBI strategies help identify and modify distorted thoughts and unhelpful behaviour [48] and promote the development of positive coping strategies, and cognitive and behavioural adaptation [47, 56]. Positive changes in the cognitive process and development of positive coping behaviour help reduce stressful feelings such as anxiety and depression and, in turn, could improve psychosocial functioning and QOL [57].

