### Sample size

The sample size was estimated using the G*Power (version 3.1.9.7) sample size calculator based on the effect size of CBI on anxiety, the primary outcome of this study. Evidence shows that the effect size of CBI ranges from 0.7 to 3.9 [43, 45, 46, 60]. Using the smallest effect size of 0.7, 80% power, 5% significance level and a potential 15% attrition rate, 80 participants (40 per group) will be recruited.

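### Whether to impute is left to a missing-value check that, with about 12 expected dropouts among 80 children, has little power to detect the dropout patterns that would bias the GEE

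*Protocol article*

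**What the plan says.** The Data analysis section of the Protocol article makes three linked statements. The analysis set follows intention to treat: "Outcome analysis will be conducted as an intention-to-treat analysis". The choice to impute depends on the data: "Missing value analyses will be conducted to determine the need for multiple imputations". The model has group, time and group-by-time terms: "A generalised estimation equation (GEE) model will be applied to determine the intervention effect between the groups". The section gives no criterion for the missing-value check and does not state the working correlation.

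The Sample size section sets the scale. It reads "Using the smallest effect size of 0.7, 80% power, 5% significance level and a potential 15% attrition rate", and concludes that "80 participants (40 per group) will be recruited". Outcomes are measured at T0 (baseline), T1 (6 weeks) and T2 (10 weeks).

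Three other places bear on why children might be lost:

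- The Background says of patients with poorly treated depression that "evidence suggests these patients are less likely to adhere to treatment".
- It also says of patients in Ethiopia: "They abandon treatment because they believe religious and spiritual therapies" or other alternatives work better.
- The Experimental group section schedules the sessions at the children's medical appointments.

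**The concern.** A preliminary look at the data chooses between two versions of the primary analysis. Such a rule is sound only if the look can reliably tell harmless from harmful missingness. With about a dozen dropouts that is doubtful, because failing to find a pattern is weak evidence that none exists.

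The branch taken when nothing is found is a GEE on the observed scores. An unweighted GEE is not valid in general when dropout depends on earlier outcome scores. How far it goes wrong depends on the working correlation. At stake is a modest but avoidable bias in the between-group difference, mainly at T2. There is also the awkwardness of a primary result whose method was settled after the data were seen.

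**Working it through.** **1. The plan's own figure.** Inputs from Sample size: d = 0.7, 80% power, 5% significance level (two-sided, from Data analysis), 15% attrition. For a two-sample t-test with n per arm, the noncentrality is d × √(n/2) on 2n − 2 df. With n = 34 this is 0.7 × √17 = 2.89 on 66 df, and power is 0.812. Allowing for attrition, 34 / (1 − 0.15) = 40 per arm, or 80 in all. The stated size reproduces.

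**2. Expected dropouts.** 0.15 × 80 = 12 lost, 68 retained.

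**3. Power to see a given difference.** Assume the check is a two-sided 5% t-test of baseline score, 12 dropouts against 68 completers. The noncentrality is δ × √(12 × 68 / 80) = 3.19δ on 78 df.

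| True difference δ (SD) | 0.3 | 0.5 | 0.7 | 0.8 | 1.0 |
|---|---|---|---|---|---|
| Power | 0.16 | 0.35 | 0.60 | 0.71 | 0.88 |

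**4. Detection by dropout pattern.** Simulation with 80 children and 15% dropout. The model is logit P(dropout) = a + log(OR) × earlier score in SD units, with a set to give the overall rate. The check is the same t-test, pooled over arms.

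| Pattern | Detected, OR 1.5 to 2.5 per SD |
|---|---|
| Same direction in both arms | 23%, 55%, 76% (at OR 1.5, 2.0, 2.5) |
| One arm only | 9-25% |
| Opposite directions by arm | 6-7% |

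The last row is close to the 5% that chance alone gives.

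**5. Shift in the T2 difference without imputation.** Assumptions: dropout after T1 depends on the T1 score, OR 2.5 per SD, correlations between visits 0.4-0.8. The share is the shift divided by the planned effect of 0.7.

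| Pattern | Independence GEE | Share of 0.7 | Exchangeable GEE |
|---|---|---|---|
| One arm only | 0.05-0.10 SD | 0.05/0.7 = 7% to 0.10/0.7 = 14% | about 0.02 SD or less |
| Opposite directions | 0.10-0.20 SD | 0.10/0.7 = 14% to 0.20/0.7 = 29% | about 0.02 SD or less |

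The two versions differ for a simple reason. With group-by-time terms, the independence version compares the raw means of the children still present at T2. A version with within-child correlation also uses the earlier scores of those who left.

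**6. A second scenario.** Dropout straight after baseline, depending on the baseline score, correlation 0.6, true effect −0.70 SD, 400 runs per setting.

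- One arm only, OR 2 to 3: independence GEE averages −0.61 to −0.78, and exchangeable or unstructured GEE −0.69 to −0.70. The check detects the pattern in 16-30% of trials.
- Both arms equally, OR 1.5 to 3: every version averages −0.69 to −0.71.

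**7. Steps 4 to 6 together.** The check works best on the pattern that does least harm to the contrast, and worst on the patterns that do most.

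**The case against.** Several counter-arguments carry weight.

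- **The plan names no test.** The 5% comparison is a modelling assumption. A missing-value analysis may also look at the amount and pattern of missingness, and the text does not say that a non-significant result rules out imputation. This stands, so the detection rates are illustrative. Even so, any check on about 12 dropouts has little information, and the text gives no criterion that would protect the choice.
- **The article is condensed.** The working correlation may be fixed in a fuller document, so its absence is not the fault raised here. The gate is different, because the article commits to it in words.
- **A reader might infer that the protocol itself ties trial dropout to distress.** It does not. One Background statement concerns depression and adherence to treatment, the other beliefs and abandonment of treatment. Neither concerns loss to trial follow-up or anxiety, the primary outcome. Entry also excludes children with evidence of psychological or psychiatric problems. The step to trial dropout is an inference from the tie between sessions and medical appointments, and a difference by arm is a further inference.
- **A reader might infer that this GEE is valid only under missing completely at random.** That is too strict. With an exchangeable or unstructured working correlation the shift was negligible in the scenarios tried.
- **A reader might infer that the check will usually lead to no imputation.** Under the modelled test that holds for the one-arm and opposite-direction patterns. It does not hold for same-direction dropout at odds ratios of 2.0 and 2.5, which is detected in 55% and 76% of trials.

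**Conclusion.** The concern holds in a limited form. The rule for imputing is badly fixed: it depends on the data, has no stated criterion, and rests on about 12 dropouts. A null finding cannot support the unimputed analysis.

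The possible bias at T2 is about 0.05-0.10 SD if dropout depends on score in one arm, and 0.10-0.20 SD if the directions are opposite. Both figures need an independence working correlation and an odds ratio of 2.5 per SD. With an exchangeable working correlation the shift is about 0.02 SD or less. The odds ratios, the between-visit correlations and the form of the check are assumptions and are not in the article.

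The Background and the scheduling of sessions make missing completely at random doubtful, but do not contradict it. Severity is low to moderate.

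**What to change.** Remove the conditional rule and name in advance one primary analysis that is valid under missing at random. Either of two options would do:

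- **Imputation in every case.** Impute by arm from the T0 and T1 scores before the GEE, whatever a missing-value analysis shows, and specify a working correlation other than independence.
- **A likelihood-based repeated-measures model.** Use all observed T0, T1 and T2 scores as responses. Children lost before T1 then stay in the model, which they would not if T0 entered only as a covariate. This also gives the intention-to-treat statement a concrete meaning for those children.

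The missing-value analysis can stay as a description of who was lost and when, without steering the primary analysis.

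The cost is a change of wording and syntax and a little more analysis work. The mixed model also relies on approximately normal residuals. No new data and no change in sample size are needed.

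### The stated GEE names no adjustment for the T0 score, so the effect is read from change scores or raw follow-up scores, and precision available from data already collected is given up

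*Protocol article*

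**What the plan says.** The Data analysis section states the outcome model in one sentence. A GEE is used to "determine the intervention effect between the groups in terms of a group, time, and group*time interaction". The section names no covariate, and it does not say which coefficient or time point carries the primary comparison.

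The Primary outcome section measures anxiety "before the intervention (T0, baseline), immediately after the intervention (T1, at 6 weeks) and one month after completion of the intervention (T2, at 10 weeks". The Secondary outcomes section puts depression and QOL on the same three occasions, and Study design describes a repeated-measures trial.

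The Sample size section is based on anxiety: "Using the smallest effect size of 0.7, 80% power, 5% significance level and a potential 15% attrition rate, 80 participants", that is, 40 per group. It gives no correlation between occasions and does not say which SD scales the 0.7. On the level of the test, Data analysis adds: "The significance level will be determined at 5% (two-sided) for all statistical tests".

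**The concern.** In a model with only group, time and their interaction, T0 can play one of two parts. On the natural reading of a three-occasion design it is one of the modelled outcomes, and the interaction at T1 compares the arms on change from T0. Otherwise it is left out, and the arms are compared on raw follow-up scores. Neither makes the best use of T0. Change scores subtract the whole T0 value when only a fraction rho of it carries forward; raw scores subtract none of it.

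Two things are at stake. The first is precision on the primary outcome in a trial of 80 children. The second is chance imbalance: randomisation is stratified by age group within hospital, not by T0 anxiety, so the arms can differ at T0 by chance, and neither unadjusted contrast corrects for that difference properly.

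**Working it through.** **Inputs.** From Sample size: effect size 0.7, power 80%, attrition 15%, 40 per group. From Data analysis: 5%, two-sided. From Randomisation: 1:1. Not in the article, so assumed: the T0-T1 correlation rho (shown as a range), equal variances at T0 and T1, and 0.7 expressed on the raw-score SD.

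**Step 1. The plan's own figure.** For a two-sample t-test (noncentral t) at d = 0.7, two-sided 5%, 33 per arm just misses 80% and 34 per arm gives 81.2%. Then 2 × 34 = 68 and 68 / 0.85 = 80. The stated total reproduces exactly, as a comparison at one time point.

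**Step 2. What the interaction estimates.** A GEE with group, time and group*time was fitted to simulated complete data. Its T1 interaction coefficient and robust standard error equalled the difference in mean change from T0 and its standard error.

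**Step 3. Relative variances at T1.**
- Change score: 2(1 - rho)
- Raw follow-up: 1
- T0-adjusted: 1 - rho^2

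Since 1 - rho^2 = (1 - rho)(1 + rho), the adjusted variance is (1 + rho)/2 of the change-score variance. That ratio is below 1 for rho below 1, and 1 - rho^2 is itself below 1 whenever rho is not 0. Adjustment therefore has the smallest variance for every rho strictly between 0 and 1. The reduction relative to change scores is 40% at rho 0.2, 25% at 0.5 and 15% at 0.7.

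**Step 4. Power with 34 evaluable per arm.** The effective d is 0.7/sqrt(2(1 - rho)) for change, 0.7 for raw follow-up, and 0.7/sqrt(1 - rho^2) with adjustment. At rho 0.3, for example, these are 0.592, 0.7 and 0.734.

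| rho | change, T1 vs T0 | raw T1 | T0-adjusted T1 |
|---|---|---|---|
| 0 | 52% | 81% | 81% |
| 0.2 | 61% | 81% | 83% |
| 0.3 | 67% | 81% | 85% |
| 0.4 | 74% | 81% | 87% |
| 0.5 | 81% | 81% | 91% |
| 0.6 | 89% | 81% | 94% |
| 0.7 | 96% | 81% | 98% |

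The change-score contrast reaches 80% at rho = 0.485. If all 40 per arm were evaluable, it would do so at 0.39.

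**Step 5. Other tests the same model allows.** With equal effects at T1 and T2 and exchangeable correlation, the joint two-degree-of-freedom interaction test had simulated power of 74% at rho 0.3 and 86% at 0.5. Under the same assumptions, the mean of T1 and T2 minus T0 gives 79% at rho 0.3, 85% at 0.4 and 91% at 0.5, and reaches 80% at about rho 0.31.

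**Step 6. Chance imbalance.** With 40 per arm, the T0 difference between arms has SD sqrt(2/40) = 0.22 outcome SDs. Given an imbalance of that size, the change-score estimate is shifted by (1 - rho) × 0.22, which at rho 0.4 is 0.13 SD, nearly a fifth of 0.7. The raw follow-up estimate is shifted the other way by rho × 0.22 = 0.09 SD. Linear adjustment for T0 removes the shift.

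**The case against.** A reader might infer from the table that the trial is underpowered, or that 80 is the wrong number. The article does not support that. The shortfall needs three things that it does not fix: 0.7 on the raw-score SD, the T1-versus-T0 interaction as the single test, and rho below about 0.49. If 0.7 is on the change-score SD, 80% holds at any rho. If the raw follow-up difference is the effect, power is 81% at any rho. Contrasts that also use T2 tolerate a lower correlation, and at rho 0.7 the gap nearly closes. All of this stands.

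A reader might also infer that T0 goes unused. On the natural reading it enters as an outcome, so the accurate statement is only that no T0 covariate is named.

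The strongest remaining objection is that a journal article condenses its plan, that covariates may be set out in a fuller document, and that a GEE with these three terms is a valid analysis of a randomised trial. The validity is granted, and nothing in the article rules out a T0 covariate. But the article does more than stay silent: it states the model and the terms through which the effect is judged. The efficiency comparison applies to that stated model, and it favours adjustment whether T0 is in the outcome vector or left out.

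**Conclusion.** The point holds as a free gain in efficiency over a stated method, not as an error in the sample size. Assuming equal variances, T0 adjustment is more precise than either reading of the stated model for any rho strictly between 0 and 1, and it removes the effect of chance T0 imbalance. Against change scores, the variance is 15% to 40% smaller over rho 0.7 to 0.2. Against raw follow-up scores, it is smaller by rho^2, for example 9% at rho 0.3 and 25% at 0.5.

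The effect on power is conditional. With 0.7 on the raw-score SD, 34 evaluable per arm and the T1 interaction as the test, power is 67% at rho 0.3 and 74% at 0.4, against 85% and 87% with adjustment. Whether the trial is in that range cannot be told from the article.

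**What to change.** In Data analysis, model the T1 and T2 scores with the child's T0 score on the same scale as a covariate, together with group, time and group*time. Take the adjusted group difference at follow-up as the intervention effect. Alternatively, keep T0 as an outcome but constrain the two arms to a common T0 mean. Apply the same form to anxiety, depression and QOL.

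In Sample size, keep the 80 children and the 80% power. Add that the calculation is a two-group comparison at one time point, and that the T0-adjusted T1 comparison at least meets it if 0.7 is on the raw-score SD. Do not state 85% to 91% as the trial's power, because those figures rest on an assumed correlation of 0.3 to 0.5.

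The cost is a change of wording and one degree of freedom per outcome. T0 is already collected, so no children or visits are added.
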